**Objective:**

This study aims to (1) identify the characteristics of adult responders and nonresponders with asthma to a behavioral intervention to increase physical activity and (2) evaluate the functional and clinical benefits in the medium term.

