**Methods:**

This prospective pragmatic study will include adults with moderate to severe asthma who enroll in a behavioral intervention. All individuals will receive an educational program and an 8-week intervention to increase PADL (1 time/wk; up to 90 min/session). The educational program will be conducted in a class setting through group discussions and video presentations. Behavioral interventions will be based on the transtheoretical model using counseling, incentives, and individual feedback aiming to increase participation in physical activity. Motivational interviewing and guidelines for overcoming barriers will be used to stimulate individuals to reach their goals. Pre- and postintervention assessments will include the following: PADL (triaxial accelerometry), body composition (octopolar bioimpedance), barriers to PADL (questionnaire), clinical asthma control (Asthma Control Questionnaire), quality of life (Asthma Quality of Life Questionnaire), anxiety and depression levels (Hospital Anxiety and Depression Scale), and exacerbations. “Responders” to the intervention will be defined as those who demonstrate an increase in the number of daily steps (≥2500).

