The World Health Organization (WHO) recommends that adults perform 150 to 300 minutes of moderate-intensity aerobic physical activity weekly to achieve certain health benefits [8]. In addition, international guidelines [9] and GINA [1] classify, with A-level evidence, people with asthma who engage in regular physical activity to reduce cardiovascular risk and improve their quality of life [1]. A previous study found that a behavioral intervention to increase PADL improves clinical asthma control, sleep quality, and anxiety symptoms in adults with moderate to severe asthma [5]. However, 17% of the individuals did not improve their physical activity level, and 25% did not improve their clinical control after the intervention. Individuals with other chronic respiratory [10], cardiac [11], musculoskeletal [12], and neurological diseases [13] have also been classified as better or worse responders to specific interventions.

Thus, despite the benefits obtained by behavioral intervention aimed at increasing PADL in adults with asthma [5], it is necessary to know the characteristics of responders and nonresponders to guide the management in a more personalized approach. Moreover, the effects of this intervention were only assessed in the short term (immediately after the intervention), and the medium-term effects remained unknown. We hypothesize that the intervention might cause different effects according to the clinical characteristics of the individuals, including asthma control, age, anxiety and depression levels, obesity, and several comorbidities. Therefore, the main objective this prospective cohort study will be to identify the characteristics of adult responders and nonresponders with moderate to severe asthma to a behavioral intervention to increase PADL and evaluate the functional and clinical responses in the short and medium terms.

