### Statistical Analysis Planning

Individuals will be stratified as “responders” and “nonresponders” based on an increase of ≥2500 steps [45]. The Kolmogorov-Smirnov test will be used to assess data normality. Cluster analysis will be used to characterize the groups according to individual characteristics. Cluster analysis will be carried out in 2 stages: hierarchical analysis using the Ward method to determine the number of clusters and k-means analysis to group the clusters [46]. Comparisons of clinical, anthropometric, and psychosocial data obtained in the responder and nonresponder groups will be conducted using the 2-tailed *t* test or Mann-Whitney *U* test for continuous variables and the chi-square test for categorical variables. To determine the independent factors associated with the level of PADL (dependent variable, considering clinical control, smoking, obesity, anxiety, and depression as independent variables), multiple linear regression analysis (stepwise forward) will be used. The intra- and between-group comparison at baseline, short term, and medium term will be assessed using the 2-way ANOVA with repeated measures test. The significance level will be adjusted to 5% (*P*<.05) for all tests. If necessary, intention-to-treat analysis will be performed, as described earlier. SPSS Statistics (version 22.0; IBM Corp) will be used for statistical analysis. Data integrity will be monitored by regularly scrutinizing data files for omissions and errors. Participants will be given an anonymous study ID to protect confidentiality, and only study investigators will have access to the final trial data set.

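### The only multivariable model takes the level of physical activity as its outcome, so the plan has no adjusted analysis of which characteristics go with response

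*Protocol article*

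**What the plan says.** The abstract's Objective is to "identify the characteristics of adult responders and nonresponders with asthma to a behavioral intervention to increase physical activity", and the Introduction repeats this as the main objective. The abstract's Methods define responders as "those who demonstrate an increase in the number of daily steps (≥2500" or more); Statistical Analysis Planning likewise splits participants "based on an increase of ≥2500 steps". Response is therefore a within-person change.

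Statistical Analysis Planning then lists four kinds of analysis:

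- **Clustering** (Ward, then k-means): "Cluster analysis will be used to characterize the groups according to individual characteristics".
- **Unadjusted comparisons** of responders with nonresponders by t, Mann-Whitney or chi-square test.
- **One regression**, introduced with "To determine the independent factors associated with the level of PADL (dependent variable", "considering clinical control, smoking, obesity, anxiety, and depression as independent variables"; the method is given as "multiple linear regression analysis (stepwise forward) will be used".
- **A two-way repeated-measures ANOVA** within and between groups at baseline, short term and medium term.

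For the regression, the section gives no time point, no change score and no baseline-steps covariate.

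**The concern.** The Introduction hypothesises that several characteristics (asthma control, age, anxiety and depression, obesity, comorbidities) shape the effect of the intervention. These may well be correlated with one another, so separating them needs an adjusted analysis. The only adjusted analysis has a different target from response.

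A characteristic can go with low activity both before and after the programme without affecting the gain. A level model would list it as an independent factor. Conversely, a characteristic that raises the gain but goes with a low starting level can be partly or wholly cancelled. The Discussion wants the results to guide referral according to a patient's likely response, so the distinction matters in use.

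**Working it through.** **1. The plan's own figure.** Inputs from Sample Size Calculation: difference 2500, SD 2500, α=5%, power 80%. The two-sided normal formula gives n = 2(1.96+0.842)²/(2500/2500)² = 15.7, so 16 per group; the t-test version gives 16.7, so 17. Then 17/0.17 = 100. The figure reproduces. It sizes an unadjusted two-group comparison and says nothing about the regression.

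**2. What each reading of level would estimate.** Write B for baseline steps, C for change, F = B + C for week-8 steps and X for a characteristic.

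- Level = B: the model contains no information on response.
- Level = F: cov(X,F) = cov(X,B) + cov(X,C), which mixes starting activity with gain.
- Level = F with B as a covariate: close to a model of change, but B is not in the stated list.

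Eligibility (under 150 min/wk of moderate to vigorous activity, or at most 7500 steps/d) still leaves baseline steps free to vary, so the mixing is not trivial.

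**3. Closed-form check.** Take B and C uncorrelated, SD(C)=2500 (the only step SD in the document) and SD(B)=2000 (assumed). Then SD(F) = √(2000²+2500²) = 3202, and r(X,F) = [r(X,B)·2000 + r(X,C)·2500]/3202. With n=100, power ≈ Φ(√97·atanh|r| − 1.96), plus the opposite tail where r is near zero.

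- X linked to baseline only (r=0.4): r(X,F) = 800/3202 = 0.250, flagged in about 71%.
- X linked to change only (r=0.3): r(X,F) = 750/3202 = 0.234, found in about 65%, against 86% if C is the outcome.
- X with −0.3 to baseline and +0.3 to change: r(X,F) = 150/3202 = 0.047, found in about 7%, against 86%.

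**4. Simulation of the same set-up** (4000 runs, one predictor; where three values appear, SD(B) = 1500/2000/2500):

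| Outcome modelled | Baseline only, r=0.4 | Change only, r=0.3 | −0.3 baseline, +0.3 change |
|---|---|---|---|
| Baseline level | 99% | 5% | 85-87% |
| Week-8 level | 55/71/82% | 74/66/57% | 18/7/5% |
| Change | 5% | 86-87% | 86% |
| Week-8 level, adjusted for baseline | 5-6% | 86-87% | 89% |

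**5. With measurement error and enrolment selection.** All of these inputs are assumed: unselected measured steps mean 7000, SD 2500; enrolled if measured baseline is at most 7500; mean true gain 2385; gain SD 1500 or 2500; reliability 0.6-0.8; n=100; level read as week-8 steps.

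| | Gain SD 1500: level | Gain SD 1500: change | Gain SD 2500: level | Gain SD 2500: change |
|---|---|---|---|---|
| Unrelated to gain, r=−0.5 with usual activity | 69-74% | 10-16% | about 49% | 8-10% |
| Predicts gain (r=0.5), r=−0.3 with usual activity | 30-37% | 66-91% | 79-82% | 95-98% |

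Repeat runs move these by a few points. Change stays somewhat above 5% for the unrelated factor because enrolment on a noisy baseline ties measured change to usual activity. At gain SD 1500, adding measured baseline steps as a covariate raises that rate to 22-39%, since an error-prone baseline does not fully account for usual activity.

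**6. Why not logistic regression on responder status.** About 17 nonresponders over five candidates is 17/5 = 3.4 per variable, too few. Continuous change suits n=100 better.

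**The case against.** The strongest reply is that the objective speaks of characteristics, not of independent predictors, and that the plan meets it directly by comparing responders with nonresponders. The regression is introduced separately and openly labelled as concerning level; nothing calls it the main analysis. A factor truly associated with level is not a false positive for a level model. Much of this stands. The responder comparisons do address the objective, and under the assumptions of step 5 (gain SD 1500) they flag the irrelevant factor in only about 6-12% of trials. They do not adjust for anything, however, so the gap remains.

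A reader might infer several stronger things that the document does not support:

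- **That response is studied only by one-at-a-time tests.** On its natural reading the repeated-measures ANOVA also uses the responder groups, because no other groups are defined. It compares outcomes over time, though, and does not estimate predictors of response.
- **That clustering ignores response.** It is said to characterise the groups. How response enters is unclear, but the link is not absent.
- **That correlates of inactivity will be published as features of nonresponders.** This is a risk of misreading; nothing in the protocol says the authors will do it.
- **That a level model must hide true predictors.** At gain SD 2500 it finds the simulated one in about 79-82% of trials.

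The reference to level may also be loose wording for change. Nothing in the article says so, and the article itself names the outcome, predictors and method, so this is a stated choice and not a detail left to a fuller plan.

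**Conclusion.** The point holds in a limited form. Response is a change, the only multivariable model has level as its outcome without a baseline-steps covariate, and so the plan contains no adjusted analysis of which characteristics go with response.

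The more robust consequence is the flagging of characteristics that mark inactive patients: about 49-74% of trials against 8-16% with change, for a factor correlated −0.5 with usual activity. The loss of power for a true predictor (about 30-82% against 66-98%) depends strongly on the gain SD, which the document does not give.

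These sizes are illustrative. They assume week-8 level and simulate one predictor instead of five-variable stepwise selection. The assumed gain also implies 54-59% responders, where the sample-size section implies about 83% (100 − 17). The mismatch itself needs none of these assumptions. Because the direct responder comparisons are already planned and no data are affected, this should be fixed, but it does not undermine the study.

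**What to change.** In Statistical Analysis Planning, make the dependent variable of the multiple linear regression the continuous change in daily steps, week 8 minus baseline. Use as predictors the baseline values of the characteristics hypothesised in the Introduction, which include age and comorbidities, neither of which is in the current list. Name the version without baseline steps as primary, and report the version adjusted for baseline steps as a sensitivity analysis. Keep the planned responder/nonresponder comparisons.

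Cost: one changed sentence; data, sample size and software stay as they are. Downside: the two versions may disagree because baseline steps are measured with error, which is why one should be named primary in advance. If a model of level is still wanted, state its time point and label it as describing activity, not response.

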### Sample Size Calculation

A minimum number of 17 individuals in at least one of the groups (responder or nonresponder) was established to detect a difference of 2500 (SD 2500) steps [45] in the primary outcome (α=5%, 1 – β=80%). A sample of 100 participants was established, considering the percentage of nonresponders (17%) as previously observed [5]. Clinical improvement in the ACQ score (≥0.5) [3,32] will be considered a secondary outcome.

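### The only multivariable model uses forward stepwise selection, omits age and comorbidity, and has PADL level rather than response as its outcome

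*Protocol article*

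**What the plan says.** The Introduction of the protocol article hypothesises that the intervention acts differently according to "clinical characteristics of the individuals, including asthma control, age, anxiety and depression levels, obesity, and several comorbidities". The Conclusions paragraph of the abstract and the Conclusion of the Discussion repeat this list.

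Statistical Analysis Planning contains one multivariable model. Its purpose is stated as "To determine the independent factors associated with the level of PADL", and its candidates and method as "considering clinical control, smoking, obesity, anxiety, and depression as independent variables), multiple linear regression analysis (stepwise forward) will be used".

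Two other planned analyses bear on the hypothesis. One is unadjusted: "Comparisons of clinical, anthropometric, and psychosocial data obtained in the responder and nonresponder groups will be conducted", by t test, Mann-Whitney or chi-square test. The other is a Ward and k-means clustering: "Cluster analysis will be used to characterize the groups according to individual characteristics". Neither lists its variables.

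No entry or removal threshold is given for the stepwise procedure. For tests in general, the section says "The significance level will be adjusted to 5" per cent.

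**The concern.** Three features of the regression sentence do not fit its stated purpose.

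- **Candidate list.** Age and a comorbidity term are in the hypothesis but not in the model. A variable that is not a candidate cannot be shown to be an independent factor, and the others cannot be adjusted for it. Age could plausibly be related to obesity, comorbidity and step count.
- **Selection.** Forward selection picks terms because they look strong in this sample and then reports their p-values as if they had been fixed in advance. A dropped factor gets no estimate and is easily read as unassociated. Anxiety and depression scores are likely to be correlated, so which of them enters may be largely chance.
- **Outcome.** The dependent variable is the level of PADL. The hypothesis and the study title concern response. A factor can be related to how active people are without being related to how much they change.

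The Discussion intends the results to guide referral of patients by their profile, so readers will give the list of independent factors weight.

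**Working it through.** **1. The two lists.**

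| Factor | Hypothesis | Regression candidate |
|---|---|---|
| Asthma control | yes | yes |
| Anxiety | yes | yes |
| Depression | yes | yes |
| Obesity | yes | yes |
| Age | yes | no |
| Several comorbidities (listed separately from the above) | yes | no |
| Smoking | no | yes |

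**2. The plan's own sample size.** The plan states: "A minimum number of 17 individuals in at least one of the groups (responder or nonresponder) was established to detect a difference of 2500" steps, with SD 2500, α 5% and power 80%. Taking the test as two-sided (an assumption), the normal approximation gives 2 × (1.96 + 0.84)² × (2500/2500)² = 15.7, so 16 per group. The exact noncentral-t power is 78.1% at 16 and 80.7% at 17, so 17 is reproduced. With 17% nonresponders, 17/0.17 = 100. This point does not change that figure.

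**3. What selection does.** The documents give no slopes, predictor correlations or entry threshold. I assume n = 100, standardised predictors with mutual correlation 0.3, residual SD 1, and entry at p < 0.05 (from the 5% level set for all tests). Ranges span independent simulation runs of 2,000 to 4,000 replicates. The last column judges the full model at p < 0.05 as well, so that like is compared with like.

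| Five candidates | Forward stepwise | Full model, all terms | Full model, significant terms only |
|---|---|---|---|
| No true effect: at least one factor found | 20–22% | – | 20–21% |
| Two or three slopes of 0.2: coverage of nominal 95% intervals | 75–81% | 95% | 78–88% |
| Two or three slopes of 0.2: each true factor found | 49–52% | – | 40–42% |
| Two or three slopes of 0.2: overstatement of those found | 51–58% | – | 53–54% |
| One slope of 0.2: coverage | 63–64% | 95% | 62% |
| Two slopes of 0.3: coverage | 85% | 95% | 88% |

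For independent tests the null rate by formula is 1 − 0.95⁵ = 22.6%. With seven terms it is 1 − 0.95⁷ = 30.2%, and 28% in simulation for the full model with correlation 0.3.

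Part of the stepwise detection rate comes from a shift in what is estimated. With two true slopes of 0.2 and correlation 0.3, the first term to enter alone has an expected coefficient of 0.2 + 0.3 × 0.2 = 0.26, because it carries some of the effect of the omitted one.

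**4. Room for a full model.** At a fixed partial correlation of 0.25, f² = 0.0625/0.9375 = 0.0667 and the noncentrality is √(100 × 0.0667) = 2.58. Power is 72.4% with five terms and 72.4% with seven. At 0.30 it is 87.5% with either. Adding baseline steps makes eight terms: 100/8 = 12.5 participants per term, with 100 − 8 − 1 = 91 residual degrees of freedom against 94 for five terms.

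**5. The unadjusted route for age.** With 17 nonresponders and 83 responders, the noncentrality for a difference of d SD is d × √(17 × 83/100) = 3.76d. Two-sided power is 46% at d = 0.5 and reaches 80% at about d = 0.76.

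**The case against.** The strongest reply is that the regression is one secondary, exploratory analysis. The primary outcome, the sample size and the responder comparison do not depend on it. That is correct and limits the weight of the point.

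Several stronger readings are tempting, and the documents do not support them.

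- A reader might infer that the age and comorbidity hypotheses go untested. The responder comparisons and the cluster analysis may include both, and an article may leave their variable lists to the full protocol. What holds is narrower: neither is in the adjusted model, and neither is named in any planned analysis.
- A reader might infer that stepwise selection causes the roughly 20% chance of a false factor, or the overstatement of more than 50%. A full model judged at p < 0.05 has almost the same rates. The full model also finds each true factor less often.
- A reader might set 75–81% coverage directly against 95%. That compares selected terms with all terms. Among significant terms only, the remaining gap is small, and with a single slope of 0.2 there is none.
- A reader might take the Discussion's Conclusion as claiming results for age and comorbidity. It only restates the hypothesis.

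It can also be said that obesity, anxiety and depression are comorbidities, although the hypothesis lists several comorbidities in addition to them. The article promises no confidence intervals for this model, so the interval argument concerns whatever the output would supply. Including smoking without a hypothesis is not an error.

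What stands is the mismatch of lists, inference that ignores selection, the absence of any estimate for dropped factors, and the wrong outcome.

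**Conclusion.** The concern holds in this limited form and the sentence should be changed. Followed as written, the model cannot yield an adjusted result for age or for a general comorbidity measure. It leaves the listed factors unadjusted for age, and it gives p-values that ignore how the terms were chosen. Because the outcome is the level of PADL, adding covariates alone would still not address differential response, even for the five factors already listed.

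The numerical size rests on assumed slopes, correlation and entry threshold. Coverage for selected terms ran from 63% to 85% across the five-candidate scenarios with true effects, and much of that shortfall is a significance filter that any model shares if only its significant terms are read. The advantage of a full model is that every prespecified coefficient is reported, has the same meaning whatever the data show, and keeps 95% coverage over all terms. The mismatch of lists and of outcome needs no assumption, since it is in the text.

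**What to change.** Delete the stepwise specification. Fit one prespecified linear model of change in daily steps, over the interval used to define responders and adjusted for baseline steps. Enter together ACQ score, age, HADS anxiety, HADS depression, BMI, smoking and a defined comorbidity measure, if one is recorded. Report every coefficient with its 95% confidence interval whether or not it is significant.

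**Cost.** The text change is one or two sentences, and 100 participants remain enough to fit the model. Nominal power per term is somewhat lower than stepwise selection appears to offer: about 41% against 50% for a slope of 0.2 in the assumed five-candidate scenario, and 39–40% in a re-run with seven terms. The comorbidity measure must be defined and collected. The article mentions medical records only as the source of baseline lung function, so the sponsor should confirm that comorbidities are available. If they are not, the plan should say that this part of the hypothesis will have no adjusted estimate. Recruitment and data collection were under way at publication, so the change should be dated and made before the outcome data are analysed.

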## Methods

### Study Design

This prospective cohort study will be conducted at a university hospital that provides specialized asthma treatment. The study protocol was developed following the SPIRIT (Standard Protocol Items: Recommendations for Interventional Trials) checklist guidelines [14], and the trial was registered at ClinicalTrials.gov (NCT05159076). The study design is illustrated in Figure 1. Individuals with asthma will be enrolled in the trial after a routine medical consultation. Baseline lung function will be checked from the medical records. Eligible participants will undergo an 8-week behavioral intervention protocol to increase PADL and reduce sedentary behavior. First, all included individuals will receive an educational program, followed by an intervention aimed at increasing physical activity. All individuals will be assessed before and after the 8-week intervention and then 16 weeks later. The outcomes assessed will include anthropometric variables, clinical asthma control, health-related quality of life, physical activity levels, anxiety and depression symptoms, exacerbations, body composition, barriers to performing PADL, and physical activity behavioral stages (Figure 1).

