### Outcome Measures

The primary outcome will be PADL (the number of steps per day) using an activity monitor (by actigraphy). Secondary outcomes will include clinical asthma control, quality of life, body composition and anthropometric data, anxiety and depression levels, asthma exacerbations, physical activity barriers, and behavioral stages for physical activity. This will be a single-blinded (outcome assessor) study in which assessments will be performed before, immediately after, and 16 weeks later.

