#### Primary Outcome: PADL

PADL will be objectively assessed using an activity monitor (ActiGraph GT9X), a device that monitors frequency, intensity, and duration [27] in real time and is considered a sensitive and reliable method [28,29]. This triaxial monitor provides measurements of the amount and intensity of PADL and the monitoring of posture [27,30] through variations in acceleration. The “counts” obtained in a given period of time are linearly related to the intensity of the patient’s physical activity in this period [29]. Individuals will be instructed to use the accelerometer, attached to the hip using an elastic belt, for 7 consecutive days. All accelerometers will be initialized to collect data in 60 “epochs” on the 3 axes using ActiLife (version 6.9.5; ActiGraph) software. The following data will be later analyzed using the same software: the number of daily steps and the time spent in sedentary, light, moderate, and vigorous states of activity. Moderate to vigorous physical activity will also be evaluated. Sedentary behavior will be assessed using the same activity monitor.

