### Strengths and Limitations of the Study

In addition to the potential to identify the characteristics of responders and nonresponders, this study will also follow up 4 months after training, considered the medium term. These results will allow us to determine if behavioral changes are maintained in the responders over time. The assessment of PADL using accelerometers as a primary outcome is a study strength because it is an objective outcome measure, thus decreasing the risk of bias. The fact that the study will be performed in only 1 hospital center can be considered a limitation.

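### Step counts define responders and are then compared between responders and nonresponders over time, so the group-by-time effect is built in and the later course is biased by regression to the mean

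*Protocol article*

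**What the plan says.** Statistical Analysis Planning forms the two groups "based on an increase of ≥2500 steps". The abstract makes clear that these are daily steps, and Outcome Measures names steps per day by accelerometer as the primary outcome.

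The same section then plans the longitudinal analysis: "The intra- and between-group comparison at baseline, short term, and medium term will be assessed using the 2-way ANOVA with repeated measures test". It applies a 5% significance level to all tests. The sentence names no outcome. Sample Size Calculation, however, sizes the study to detect a 2,500-step difference in the primary outcome and counts the minimum number in the responder or nonresponder group. Steps are therefore evidently meant to be compared between these groups.

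On timing, Study Design says: "All individuals will be assessed before and after the 8-week intervention and then 16 weeks later". Each visit yields one recording, with the device "attached to the hip using an elastic belt, for 7 consecutive days". Table 2 schedules one step measurement before the intervention, at enrollment. There is no control group.

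Strengths and Limitations of the Study states the intended inference: "These results will allow us to determine if behavioral changes are maintained in the responders over time".

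**The concern.** The groups are defined by the change in the variable on which they are later compared. Every responder has an observed change of at least 2,500 steps and every nonresponder has less. A group-by-time test on steps therefore finds what the grouping put there.

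The medium-term comparison has a second problem. A patient passes the 2,500-step rule partly through real change and partly through a chance-high recording at week 8 or a chance-low one at baseline. The week-8 part does not recur at follow-up. Responders then fall on average and nonresponders rise, even if nobody's true activity changes after week 8.

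Medium-term benefit is the second stated objective, and the article wants its results to guide referral. A spurious fade in responders, or a spurious late response in nonresponders, would feed into that advice.

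**Working it through.** **The plan's own figure.** For a 2,500-step difference with SD 2,500, two-sided 5% and 80% power, the normal approximation gives 15.7 per group. The t-based calculation gives 17 (power 0.807; 16 gives 0.781). Then 17/0.17 = 100. The sample size reproduces, so the fault lies in the comparison and not in this arithmetic.

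**Inputs.** From the documents: the 2,500-step cut, three visits, N = 100, 17% nonresponders. Assumed: responder status is read at week 8 against baseline; error is normal and independent between visits; the true gain is fully kept to follow-up. The documents give no within-person SD. The 2,500 in the sample size paragraph is not said to be the SD of within-patient change, so using it that way is an assumption, varied below.

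**Formula.** Let p be the nonresponder share, z its normal quantile, φ the normal density, S the SD of observed change and s the error SD at one visit.
- Responders' false fall after week 8 = (s²/S) × φ(z)/(1 − p)
- Nonresponders' false rise after week 8 = (s²/S) × φ(z)/p

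If all patients share one true gain, S² = 2s², so s²/S = S/2.

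**At 17% nonresponders, S = 2,500.** z = −0.954 and φ(z) = 0.253. The common gain that puts 17% below 2,500 is 2,500 + 0.954 × 2,500 = 4,885.
- Responders' fall: 1,250 × 0.253/0.83 = 381
- Nonresponders' rise: 1,250 × 0.253/0.17 ≈ 1,861

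**At about half nonresponders, S = 2,500.** The Introduction describes the earlier 17% as patients whose activity level did not improve, which is not the same as a gain below 2,500. If it means a change of zero or less, the mean gain is 0.954 × 2,500 = 2,385 and about 52% fall below 2,500. Then z = 0.046 and φ(z) = 0.3985.
- Responders' fall: 1,250 × 0.3985/0.482 ≈ 1,030

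**Simulation**, 4,000 trials of N = 100 per row, steps gained from baseline, true gain fully kept:

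| Assumption | Nonresponders | Responders, week 8 → follow-up | False fall | Fall significant | Nonresponders' false rise |
|---|---|---|---|---|---|
| S = 2,500, same gain in all | 17% | 5,645 → 5,259 | 387 (7%) | 31% | 1,846 |
| S = 2,500, same gain in all | 50% | 4,491 → 3,488 | 1,003 (22%) | 85% | 996 |
| S = 2,500, same gain in all | 52% | 4,449 → 3,416 | 1,033 (23%) | 87% | 956 |
| S = 2,500, half of change variance real | 17% | 5,650 → 5,466 | 184 (3%) | 17% | 937 |
| S = 2,500, half of change variance real | 50% | 4,491 → 3,992 | 499 (11%) | 53% | 492 |
| s = 500 (S = 707), same gain in all | 17% | 3,389 → 3,281 | 108 (3%) | 31% | 526 |
| s = 500 (S = 707), same gain in all | 50% | 3,064 → 2,782 | 282 (9%) | 85% | 283 |

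The group-by-time test was significant in 100% of trials in every row. In the rows with one common gain there is no real difference between the groups to find. As a control, the first row's model with 83/17 labels unrelated to steps rejected in 4.9% of trials, so the grouping is the cause.

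**The case against.** The ANOVA sentence names no outcome, and the second objective speaks of functional and clinical benefits. For the ACQ, AQLQ and HADS, groups formed on steps are not circular in this direct way. That stands, and the point is confined to steps and, through correlation, other accelerometer measures. For steps, the sample size paragraph makes the intention clear enough. The omission cannot be put down to an unseen analysis plan, because the article itself fixes the grouping rule, the test and the inference.

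The size is uncertain. A reader might take a loss of nearly a quarter of the gain, significant in some 85% of trials, as the expected result. The documents do not support that. It needs about half nonresponders and a change SD of 2,500 that is all noise. At the plan's own 17% the responder loss is about 7% or less, although the nonresponders' false rise is then large.

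A reader might also infer that responders must appear to decline whatever really happens after week 8. That is too strong. Regression to the mean is an added bias, and a real further gain larger than the bias would still show as a gain. Carrying the most recent assessment forward, as Analysis of the Population prescribes, sets the later change to zero for patients lost after week 8. This dilutes the artefact without removing it.

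Finally, this point leaves the main objective, the characteristics of the two groups, untouched. The maintenance sentence stands in the Discussion, and Contribution and Clinical Applicability puts the same question for patients with moderate to severe asthma in general. This narrows what has to change, but not the need to change it: the between-group test at 5% is in the Methods.

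**Conclusion.** The concern holds for steps per day. The group-by-time test between groups formed on steps is uninformative, since it was significant in every simulated trial even when all patients responded alike. Maintenance judged within responders is biased downward, and the later course of nonresponders upward.

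The direction follows from the grouping rule and ordinary week-to-week error. The size rests on an unstated within-person SD and on the true nonresponder share. With an assumed change SD of 2,500 and a common, fully kept gain, the false responder loss runs from about 380 steps (17% nonresponders) to about 1,030 (about half). It is about 110 to 280 at a within-person SD of 500, and about 180 to 500 if half of the change variance is real. The wider readings, that the clinical questionnaires are equally circular or that a decline will be seen regardless of the truth, are not supported.

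**What to change.** - In Statistical Analysis Planning, exclude steps and the other accelerometer measures from the responder-versus-nonresponder ANOVA. Show step trajectories by group as description only, with a note on regression to the mean.
- Assess maintenance of steps in the whole cohort, as the change from week 8 to the 16-week follow-up with a 95% confidence interval. This contrast is free of the responder selection.
- Report whole-cohort change from baseline at both visits, with a caveat. Entry may rest on 7,500 steps a day or fewer, and only one step measurement is scheduled before the intervention, so selection on a low baseline may inflate that change.
- In Strengths and Limitations of the Study, replace the claim about maintenance in responders with one about maintenance in the cohort.

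The cost is that the responder-specific maintenance claim is no longer tested. Only analysis and discussion wording changes; visits, patients and intervention stay as they are.
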